## Abstract

**Background:**

Major Depressive Disorder (MDD) is a psychiatric disorder with a highly recurrent character, making prevention of relapse an important clinical goal. Preventive Cognitive Therapy (PCT) has been proven effective in preventing relapse, though not for every patient. A better understanding of relapse vulnerability and working mechanisms of preventive treatment may inform effective personalized intervention strategies. Neurocognitive models of MDD suggest that abnormalities in prefrontal control over limbic emotion-processing areas during emotional processing and regulation are important in understanding relapse vulnerability. Whether changes in these neurocognitive abnormalities are induced by PCT and thus play an important role in mediating the risk for recurrent depression, is currently unclear.

In the Neurocognitive Working Mechanisms of the Prevention of Relapse In Depression (NEWPRIDE) study, we aim to 1) study neurocognitive factors underpinning the vulnerability for relapse, 2) understand the neurocognitive working mechanisms of PCT, 3) predict longitudinal treatment effects based on pre-treatment neurocognitive characteristics, and 4) validate the pupil dilation response as a marker for prefrontal activity, reflecting emotion regulation capacity and therapy success.

**Methods:**

In this randomized controlled trial, 75 remitted recurrent MDD (rrMDD) patients will be included. Detailed clinical and cognitive measurements, fMRI scanning and pupillometry will be performed at baseline and three-month follow-up. In the interval, 50 rrMDD patients will be randomized to eight sessions of PCT and 25 rrMDD patients to a waiting list. At baseline, 25 healthy control participants will be additionally included to objectify cross-sectional residual neurocognitive abnormalities in rrMDD. After 18 months, clinical assessments of relapse status are performed to investigate which therapy induced changes predict relapse in the 50 patients allocated to PCT.

**Discussion:**

The present trial is the first to study the neurocognitive vulnerability factors underlying relapse and mediating relapse prevention, their value for predicting PCT success and whether pupil dilation acts as a valuable marker in this regard. Ultimately, a deeper understanding of relapse prevention could contribute to the development of better targeted preventive interventions.

**Trial registration:**

Trial registration: Netherlands Trial Register, August 18, 2015, trial number NL5219.

## Background

### Rationale

Major Depressive Disorder (MDD) is the most prevalent psychiatric disorder, with a lifetime prevalence of 19% [1] and a highly recurrent nature [2, 3]. History of recurrence is an important predictor of relapse [4, 5], making prevention of relapse early in the course of the disease an important clinical goal. Understanding the mechanisms facilitating relapse can give insight into the core processes essential for relapse prevention, and may provide markers to guide clinicians in selecting preventive strategies [6].

One way of gaining a better understanding of relapse vulnerability is investigating the neurocognitive mechanisms of existing therapeutic interventions that proved effective in preventing relapse [7, 8]. Clinically, cognitive therapy during the depressive episode has been shown to have an enduring preventive effect [9–11]. Applying preventive cognitive therapy (PCT; a cognitive-therapy based psychological intervention) in the remitted state has shown effectivity in lowering relapse-risk up to 10 years, compared to both no therapeutic interventions and to (tapering) maintenance antidepressant use [12–17]. Studying the working mechanisms of PCT can provide insight into which cognitive and affective processes put an individual at risk for relapse, and which changes therein mediate a lowered vulnerability risk following treatment.

Studies in the acute phase of MDD have shown that cognitive therapy affects neurocognitive functioning, including lowering cognitive biases [18, 19] and increasing prefrontal cortical control over limbic structures during emotional processing [20–22]. These processes are thought to lay at the core of the pathophysiology of MDD [23–29], and might add to the development and perpetuation of depression through overrepresentation and overinterpretation of negative information and negative affect [23, 30–33]. Several studies have shown that abnormalities in the prefrontal cortex persist in the remitted phase of MDD [34–37] and may predict disease course [38–43]. Furthermore, abnormal prefrontal regulation has been related to specific MDD typical cognitive processes [23, 44–49] that may persist after remission and have been linked to recurrence, such as cognitive biases towards negative information [49–51], heightened cognitive reactivity to stressful situations [52–54], negative rumination [55–58], affective reactivity [59], and inadequate emotion regulation (reflected in an increased tendency to engage in, and difficulty to disengage from, negative mood states) [32, 60, 61]. Whether the protective effect of PCT is obtained via alternations in these neurocognitive processes and how individual differences therein hamper such effect is yet unknown.

Though often neglected, difficulties in processing reward and maintaining positive emotions may similarly contribute to relapse vulnerability in MDD. Abnormalities in processing positive emotions have been consistently associated with MDD, also in the remitted phase [37, 62–68]. Moreover, neural responsivity in regions important for reward processing has been related to a history of depressive episodes [69] and both psychological and pharmacological treatment response [70]. In acute MDD, difficulties sustaining positive emotions have been suggested to reflect reduced fronto-striatal capacity [71, 72]. In remitted MDD, Matsubara and colleagues [73] found abnormal fronto-limbic activity during effortful regulation of positive emotions, while others did not [61, 74]. Whether PCT obtains part of its preventive effects by impacting neurocognitive processing of positive emotional material, is not yet known.

### Aims

In the Neurocognitive Working Mechanisms of the Prevention of Relapse In Depression (NEWPRIDE) study, the neurocognitive mechanisms of preventive therapy will be investigated using a within-subject longitudinal comparison of cognitive biases and fMRI characteristics related to positive and negative emotion processing before and after PCT, as compared to a waiting list control group. At baseline, a healthy control (HC) group will be included for cross-sectional comparison of residual abnormalities.

The present study has four main aims. Firstly, we aim to cross-sectionally examine whether cognitive biases and functional magnetic resonance imaging (fMRI) responses during the regulation of positive and negative emotions in medication-free, highly recurrent, remitted MDD (rrMDD) patients differ from controls. We hypothesize residual abnormalities in rrMDD patients compared to HC in (i) an amygdala-insular-subgenual anterior cingulate cortex (ACC)-ventrolateral prefrontal cortex (PFC) circuitry associated with biased processing of negative emotional information, (ii) a striatal-medial PFC circuitry associated with biased processing of positive emotional information, and (iii) the lateral-and medial PFC circuitry associated with cognitive control [75].

Secondly, this randomized controlled fMRI-study is the first to investigate the neurocognitive working mechanisms of PCT (compared to a waiting list condition) in rrMDD patients. We hypothesize that PCT will result in increased lateral and medial prefrontal activation, dampened activation of limbic regions, and improved connectivity between these regions during emotion regulation, which will coincide with normalised processing and regulation of negative information and a lowered likelihood of a prevailing negative mood. Furthermore, we hypothesize that increased PFC activation following PCT relates to increased preferential processing of positive information [70, 76].

Thirdly, we aim to identify pre-treatment neurocognitive markers predictive of long-term PCT success measured at 18-month follow-up. It is expected that low pre-treatment insular and PFC activation [39, 77] and low PFC connectivity with emotion processing areas during emotion processing predicts favourable treatment response [78]. Also, we hypothesize that participants with larger pre-post differences on neurocognitive measures, will show lowest relapse up until18-month follow-up.

Finally, we aim to investigate the value of the pupil dilation response (PDR) as a new predictor of frontal regulatory efforts during emotion regulation and PCT effects as a means of providing cheaper, non-imaging, yet imaging-informed, neurocognitive markers of treatment-success in rrMDD [79–81]. We hypothesize that increased PFC activation following PCT will be reflected in an increased PDR during emotion regulation, and that low pre-treatment PDR-response during emotional regulation will be predictive of PCT effects.

### Design

NEWPRIDE is an open-label randomized controlled trial (RCT), consisting of four phases following an initial screening: [1] a baseline clinical, neuropsychological, fMRI- and PDR-examination (T0) [2]; a three-month treatment phase, including either eight sessions PCT or a waiting-list control period [3]; a post-treatment clinical, neuropsychological, fMRI- and PDR-examination (T1) 3 months after baseline, and [4] a follow-up clinical examination (T2) 18 months after baseline. A flowchart of the study design is provided in Fig. 1.

**Fig. 1 Fig1:**
[figure not shown]
Flowchart providing an overview of the NEWPRIDE study design

### Participants

#### Recruitment

For this study, 75 rrMDD patients will be recruited, plus 25 HC participants, matched for age, sex, and education level. We will recruit rrMDD patients who have been in remission for over 2 months and who are highly recurrent (meaning having experienced two or more depressive episodes in the past 5 years). Given that this population is often no longer in care after remission, we will primarily recruit via advertising and (social) media.

#### Inclusion and exclusion criteria

Criteria for inclusion for all participants are:
Age 18 to 60 years;Normal intelligence (IQ > 85), as assessed with the Dutch Adult Reading Test, or indicated by having finished an education on at least vocational level;(Near) native Dutch language proficiency;No current DSM-IV diagnosis, according to the Structured Clinical Interview for DSM-IV Axis I disorders (SCID-I);No current depressive symptomatology, as indicated by a score of 13 or less on the Inventory of Depressive Symptomatology (IDS-SR) at the time of inclusion;No past or present alcohol or drug dependency;No general MRI contra-indications.

We apply the following criteria specific for the rrMDD group:
Meeting the lifetime criteria of a DSM-IV MDD diagnosis, according to the SCID-I;Currently in remission from the last Major Depressive Episode (MDE) for more than 2 months, but not longer than 2 years, according to the DSM-IV criteria;At least two MDE’s in the past 5 years;No regular use of psychotropic medication, including anti-depressant medication, for at least 4 weeks;No cognitive (behavioural) therapy for the last MDE;No current or past psychotic or manic/hypomanic episode, nor any DSM-IV developmental disorder diagnosis.

Finally, an additional criterion for HC participants is:
Absence of a lifetime diagnosis of any DSM-IV disorder, as assessed with the SCID-I.

#### Sample size

A total of 100 participants will be included, of which 75 rrMDD patients and 25 HCs. Power analyses for behavioural data, performed with G*Power 3.9.1.4, show that groups of 25 are sufficient to detect moderate effects (with 80% power and α = 0.05) for both cross-sectional group comparisons and longitudinal treatment effect analyses. Exact power analyses for fMRI analyses are difficult, due to the complex mass univariate nature of the data. However, previous comparable imaging studies yielded sufficient power with the inclusion of 20 participants per group [21, 37, 64, 70, 78, 82, 83]. We will include a minimum of 25 (carefully selected) participants per group, to allow for loss of data due to follow-up drop-outs.

The inclusion of 75 rrMDD patients allows for several lines of analysis. Firstly, cross-sectional comparisons will be carried out in 50 rrMDD patients versus 25 HCs in order to establish residual abnormalities in emotion processing. Because of an (unforeseen at the time of planning of the study) replacement of the MRI scanner, the last included 25 rrMDD patients (all allotted to the treatment condition) will be scanned on a different scanner, and will therefore not be included in this analysis. Secondly, longitudinal analyses of immediate treatment effects will be performed in the first 50 rrMDD patients who were randomized to either the therapy group or the waiting list control (25 vs. 25). Finally, since it is expected that 50% of rrMDD patients relapses within 1,5 years [41, 59], an additional group of 25 rrMDD patients will be included for the PCT condition, expanding the group of participants receiving treatment to *n* = 50 to allow analyses of pre-post differences in relation to clinical outcome at 18-month follow-up. Even though these last 25 patients will be scanned on a different MRI scanner, we will ensure that all participants have their pre- and post-treatment scanning session on the same MR machine.

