### Statistical analyses

#### Questionnaire and behavioural data

Cross-sectional residual characteristics of remitted MDD will be tested with a (Repeated Measures-, in case of highly correlated task conditions) AN(C) OVA procedure. The effects of PCT as measured with questionnaires and cognitive tests before and after treatment will be analysed within a multi-level analysis framework. Appropriate nonparametric tests (e.g. Friedman test) will be used if warranted. Effects will be considered significant at *p* < .05. Age, sex, and education level will be added as covariates.

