A methodological difficulty of the follow-up design is the risk of participants dropping out, a risk enlarged by the expected amount of relapse. If possible, participants who drop out will be replaced. For the longitudinal analysis, the number of included participants will be sufficient to allow for an estimated 20% loss of participants and to detect an expected medium-sized within-group treatment effect. Furthermore, the fact that the last group of participants is scanned on a different MR-scanner might lead to higher between-group variance. Fortunately, the scanner change only affects the longitudinal analyses of PCT success prediction in the treatment condition. Since we anticipate a 50% relapse in both first-scanner and second-scanner participant group, and because pre- and post-treatment scanning is performed on the same scanner in all participants, we expect that any effect of the scanners will be equally divided between the relapse- and no-relapse groups, thereby minimizing possible limiting effects of the scanner change.

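### The stated 80% power for moderate effects with groups of 25 is not reached for the patient-versus-control contrast at d = 0.5, and for PCT versus waiting list it depends on an unstated effect metric

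*Protocol article*

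**What the plan says.** The Sample size section reports a G*Power calculation for the behavioural data. It concludes that "groups of 25 are sufficient to detect moderate effects" ("with 80% power and α = 0.05"), and applies this "for both cross-sectional group comparisons and longitudinal treatment effect analyses". It does not give the effect size, its metric, the sidedness, the test family or a pre-post correlation.

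The same section fixes the comparisons. For residual abnormalities, "cross-sectional comparisons will be carried out in 50 rrMDD patients versus 25 HCs". For immediate treatment effects, the first 50 patients are "randomized to either the therapy group or the waiting list control (25 vs. 25").

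Under Questionnaire and behavioural data, the cross-sectional test is AN(C)OVA, with repeated measures kept for highly correlated task conditions. The longitudinal test is described so: "The effects of PCT as measured with questionnaires and cognitive tests before and after treatment will be analysed within a multi-level analysis framework".

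The Discussion says that the longitudinal sample is large enough "to allow for an estimated 20% loss of participants and to detect an expected medium-sized within-group treatment effect". The second aim, in the Aims section, compares PCT with a waiting list.

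**The concern.** Twenty-five per group is well short of what a two-group comparison of means usually needs for a standardised difference of 0.5, yet the article states 80% power without qualification. The cognitive-bias measures are among the primary outcomes, and their sensitivity rests on this one sentence. If it is too favourable, a reader of a null result may give it more weight against a moderate abnormality, or a moderate PCT effect, than the design can bear.

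The Discussion adds a mismatch of target. A within-group change in the PCT arm does not separate the effect of PCT from time, retesting or regression to the mean. The waiting list is there for that purpose.

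**Working it through.** **Inputs from the article.** Power 80%; α = 0.05; 25 per group in the power sentence; 50 vs 25 for the cross-sectional analysis; 25 vs 25 for PCT versus waiting list; 20% loss, which leaves 25 × 0.8 = 20 per arm if nobody is replaced.

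**Assumptions, not in the article.** Moderate means d = 0.5 for a mean difference, or f = 0.25 in ANOVA terms; tests are two-sided unless noted; the pre-post correlation r is shown over a range. Power is from the noncentral t or F distribution.

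**1. Cross-sectional contrast.** The noncentrality is d × √(n₁n₂/(n₁+n₂)).
- 25 vs 25: 0.5 × √12.5 = 1.77, power 41% (one-sided 54%).
- 50 vs 25: 0.5 × √16.67 = 2.04, power 52% (one-sided 65%).
- 80% at d = 0.5 needs 64 per group.
- Smallest effect detectable at 80%, two-sided: d = 0.81 for 25 vs 25 and d = 0.70 for 50 vs 25.

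Averaging m task conditions with mutual correlation ρ multiplies the effect by 1/√((1+(m−1)ρ)/m).
- 25 vs 25, ρ = 0.8, 2 to 6 conditions: 45% to 48%.
- 50 vs 25, ρ = 0.8, 2 to 4 conditions: 57% to 59%.
- 50 vs 25, ρ = 0.5, 4 conditions: 72%.

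The stated 80% is not reproduced for the group contrast by either sidedness, by either allocation, or by repeated measures on highly correlated conditions.

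**2. PCT versus waiting list: the route that reproduces the stated figure.** For a group-by-time interaction with two time points, λ = f² × N × 2/(1−r).
- N = 50, f = 0.25, r = 0.5: λ = 0.0625 × 50 × 2/0.5 = 12.5, power 93%.
- N = 50 at r = 0.3 and 0.7: 83% and 99%.
- N = 40 at r = 0.3, 0.5 and 0.7: 74%, 87% and 98%.

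What f = 0.25 means here: in a 2 × 2 layout each cell departs from additivity by f SDs, so the difference in change between arms is 4 × 0.25 = 1.0 raw SD. As a check, a t-test on change at r = 0.5 has effect 1.0/√(2(1−0.5)) = 1.0 and noncentrality 1.0 × √12.5, whose square is the same 12.5.

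**3. PCT versus waiting list: a between-arm effect of 0.5 raw SD.** With baseline adjustment the effective size is 0.5/√(1−r²), which is 0.577 at r = 0.5 and 0.700 at r = 0.7.

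| r | 25 per arm | 20 per arm |
|---|---|---|
| 0.3 | 44% | 37% |
| 0.5 | 52% | 43% |
| 0.7 | 68% | 58% |
| 0.8 | 82% | 73% |

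Power of 80% needs r of about 0.79 with 25 per arm and about 0.84 with 20. On change scores without baseline adjustment, power with 25 per arm is 41% at r = 0.5 and 61% at r = 0.7.

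The between-arm difference detectable at 80% is the unadjusted value (0.809 for 25 per arm, 0.909 for 20) times √(1−r²):
- 25 per arm: 0.809 × 0.866 = 0.70 SD at r = 0.5; 0.809 × 0.714 = 0.58 SD at r = 0.7.
- 20 per arm: 0.909 × 0.866 = 0.79 SD at r = 0.5; 0.909 × 0.714 = 0.65 SD at r = 0.7.

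**4. The within-group effect in the Discussion.** A paired t-test at a standardised change of 0.5 has power 67% with n = 25, 56.5% with n = 20 and 87% with n = 40. None of these is the power of the PCT-versus-waiting-list comparison.

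**The case against.** The article never says what moderate means, so d = 0.5 is the reader's assumption. Under a standard G*Power routine the longitudinal claim is met at ordinary correlations, and with 40 completers it is still met at r = 0.5. A group-by-condition interaction in the cross-sectional data would also pass: f = 0.25 with ρ = 0.5 and N = 50 gives 93%. A repeated-measures main effect over nearly uncorrelated conditions could pass too; three uncorrelated conditions with 25 vs 25 give 85%. An article may leave the test family and the correlation to the full protocol.

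Much of this stands. A reader might infer that the 80% is simply false for both analyses. The article does not support that for the longitudinal half, because one conventional calculation reproduces it. What remains there is that the calculation calls a 1.0 SD difference in change moderate and the article does not say so. The cross-sectional rescue is weaker: the claim is made for group comparisons, an interaction is a different effect, and the analysis section reserves repeated measures for highly correlated conditions, where averaging gains little.

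A reader might also infer that the Sample size section and the Discussion contradict each other on drop-out, one resting power on 25 and the other letting the same 25 absorb 20% loss. They do not. The Sample size section itself sets 25 as a minimum chosen with drop-out in mind, and the Discussion adds replacement where possible.

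Finally, the Discussion's within-group phrase may refer to the enlarged PCT group of 50. Then 20% loss leaves 40 and 87% power at a standardised change of 0.5. That is a reason to clarify the wording, but it still does not support the between-arm aim.

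**Conclusion.** The point holds in two parts of different strength. For the cross-sectional group contrast, the stated 80% is not delivered at d = 0.5: power is 41% for 25 vs 25 and 52% for the planned 50 vs 25. For PCT versus waiting list, the figure cannot be called wrong, but it holds only for a difference in change near 1.0 SD or a pre-post correlation of about 0.8 or more. It would be too strong to say that the trial misses any moderate effect about half the time or more. At r = 0.7 a 0.5 SD between-arm effect is missed 32% of the time with 25 per arm and 42% with 20. Separately, and without any assumption on effect size, the Discussion's within-group justification does not match the between-arm comparison of the second aim. The power figures rest on d = 0.5 or f = 0.25 and on the assumed correlations, none of which the article gives.

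**What to change.** In the Sample size section, replace the power sentence with what the design can detect at 80% power, two-sided α = 0.05:
- d = 0.70 for 50 rrMDD patients versus 25 healthy controls;
- for PCT versus waiting list, the effect metric, the assumed pre-post correlation and the between-arm difference that follows, about 0.6 to 0.8 SD for 20 to 25 completers per arm at r = 0.5 to 0.7. If the interaction convention f = 0.25 was used, say so and give its equivalent of 1.0 SD in change.

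In the Discussion, reconcile the within-group wording with the second aim by giving the between-arm figure after 20% loss: 0.65 to 0.79 SD with 20 per arm over the same correlations. If the phrase was meant for the enlarged PCT group, state that separately.

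The change is to wording only. Its one cost is a less favourable statement of sensitivity. It needs no extra patients and no change to allocation, endpoints or analysis.

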#### MRI data

Quality of BOLD fMRI data will be extensively checked, before data will be pre-processed according to standard recommended procedures. Subsequently, data will be modelled on the subject level using onsets/duration for the different task conditions, or time-course information. On the second level, between-group comparisons will be performed in order to analyse residual abnormalities in emotion regulation capacity, verbal working memory performance and resting state-perfusion and functional connectivity. A multilevel analysis model will be set up to test for the effects of treatment on these measures. Furthermore, linear modelling will be applied to identify and test the predictors of long-term treatment success, as defined by symptomatology (at T0, T1, T2) and relapse status and course (T1-T2) in the larger sample of remitted patients who have received therapy. Multivariate pattern analysis will be performed to evaluate the predictive value of post-treatment characteristics and pre-treatment changes for long-term treatment success. Effects will be considered significant at *p* < .05, corrected for multiple comparisons.

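### The fMRI group size rests on precedent alone; for the randomised comparison the margin covers drop-out only, and 20 per arm has low power for a moderate effect

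*Protocol article*

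**What the plan says.** The formal power calculation in the Sample size section is confined to behavioural data: groups of 25, moderate effects, 80% power, α = 0.05. For imaging the section says "Exact power analyses for fMRI analyses are difficult, due to the complex mass univariate nature of the data" and then relies on precedent: "previous comparable imaging studies yielded sufficient power with the inclusion of 20 participants per group". The step from 20 to 25 is explained as follows: "We will include a minimum of 25 (carefully selected) participants per group, to allow for loss of data due to follow-up drop-outs".

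The Discussion puts a figure on the loss. It describes the longitudinal numbers as enough "to allow for an estimated 20% loss of participants and to detect an expected medium-sized within-group treatment effect", and adds "If possible, participants who drop out will be replaced".

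Under Statistical analyses, MRI data, "Quality of BOLD fMRI data will be extensively checked" before pre-processing. Treatment effects are tested in a multilevel model, and significance is p < .05 after correction for multiple comparisons. Under Primary outcome measures, BOLD response is one of three primary domains, and its change after PCT is a main study parameter.

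**The concern.** Power belongs to a design measured against a specified effect and threshold, and the protocol states neither for BOLD. That earlier studies of a given size reported findings does not show that the size was adequate. With 20 per group, an observed d must exceed 0.64 to reach even uncorrected p < .05, so significant results from studies of that size tend to show large effects.

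The margin is also narrow. Drop-out at the plan's own rate uses all of it, yet the plan foresees a second kind of loss, scans that fail quality checks, and makes no stated allowance for it.

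At stake is how the main mechanistic result is read. If the imaging sample is described as sufficient, a null effect of PCT on BOLD could be taken as evidence against a prefrontal or limbic mechanism when the comparison could easily have missed a moderate one.

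**Working it through.** **1. The plan's own figure.** Inputs: 20 per group and 25 per group (Sample size); 20% loss (Discussion). 20 / (1 − 0.20) = 25, and 25 × 0.80 = 20. The figure reproduces, with no reserve beyond drop-out.

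**2. Unusable scans.** The protocol gives no failure rate. If 5% to 10% of scans fail (my assumption), participants with both scans usable number 25 × 0.80 × 0.95² = 18.05 to 25 × 0.80 × 0.90² = 16.2 per arm. The detectable d at 18 and 16 per arm is 0.96 and 1.02, uncorrected.

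**3. Power at 20 per arm.** Assumptions: two-sided tests; moderate means d or dz = 0.5, in SDs of the measure analysed; thresholds .05 and .05/3. The second threshold assumes one test for each of the three circuits in the Aims section and is used only to illustrate a mild correction.

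- Two groups: noncentral t with δ = d × √(n₁n₂/(n₁+n₂)). For 20 vs 20, δ = 0.5 × √10 = 1.58, df 38, critical t 2.02 and 2.50.
- Within group: δ = dz × √n = 0.5 × √20 = 2.24, df 19, critical t 2.09 and 2.63.
- Group-by-time interaction: noncentral F with λ = f² × N × m / (1 − ρ). With f = 0.25, N = 40, m = 2 times and ρ = 0.5, λ = 0.0625 × 40 × 2 / 0.5 = 10, df 1 and 38.
- Baseline 50 vs 25: δ = 0.5 × √(1250/75) = 2.04, df 73.

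| Comparison | Effect | Power at .05 | Power at .05/3 | d for 80% power at .05 | d for 80% power at .05/3 |
|---|---|---|---|---|---|
| PCT vs waiting list, 20 vs 20 | d = 0.5 | 34% | 19% | 0.91 | 1.06 |
| Within one arm, n = 20 | dz = 0.5 | 56% | 37% | | |
| Interaction, 20 + 20, ρ = 0.5 | f = 0.25 | 87% | 74% | | |
| Baseline, 50 vs 25 | d = 0.5 | 52% | 35% | 0.70 | 0.81 |

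**4. What f = 0.25 means.** In a 2 × 2 layout the interaction shifts each cell mean by 0.25 SD, so the arms differ in change by 4 × 0.25 = 1.0 SD. At ρ = 0.5 the SD of change is √(2 × 0.5) = 1 SD, so this is d = 1.0 on the change score. As a check, 1.0² × 20/2 = 10 = λ.

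**5. Sensitivity to the scale of d.** If d = 0.5 refers to the raw measure and ρ runs from 0.3 to 0.7, the standardised effect is 0.5/√(2(1−ρ)) for change scores and 0.5/√(1−ρ²) with baseline adjustment. Uncorrected power at 20 per arm is then 0.255 to 0.512 and 0.365 to 0.578. None of these reaches 80%.

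**6. All PCT patients.** The 50 patients allotted to PCT, less 20%, leave 40. Power for a within-group dz of 0.5 is then 87% uncorrected and 74% at .05/3. This analysis has no waiting-list comparison.

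**The case against.** Several objections have force.

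- **No standard is set for BOLD.** The moderate-effect claim is made for behavioural data, and the protocol admits that imaging power is hard to compute. A reader might infer that the design is simply underpowered for fMRI. The document does not support that flat reading: without a stated effect and threshold, the answer turns on assumptions, and some favourable ones give 87% uncorrected. What stands is that sufficiency is asserted and not shown, and that it fails for a moderate between-group effect.
- **Much harsher figures could be produced** by assuming a voxel threshold such as p < .001. The protocol names no voxel, cluster or regional method, so they are not relied on here.
- **The margin is softer than the arithmetic suggests.** The 25 is a minimum, drop-outs are replaced where possible, and a multilevel model can keep a participant with one usable scan. The precedent is also a count of participants included, not necessarily of scans passing quality control. So it goes too far to say that nothing at all is left for unusable scans. But replacement is conditional and named for drop-outs only, and no allowance for failed scans is stated.
- **The scope is limited.** The 20% loss is given for the longitudinal analysis. The baseline contrast has 25 controls, five above the figure of 20, and no follow-up loss.
- **The cited imaging studies are not at hand.** Whether any reported a power calculation cannot be checked. The point is that the protocol carries over no effect size or threshold from them.

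**Conclusion.** The concern holds for the randomised 25 versus 25 BOLD comparison. Precedent is its only sample-size support, and the move from 20 to 25 is used up by the plan's own drop-out rate. At 20 per arm, power for a moderate between-group effect is 34% uncorrected and 19% at .05/3; the plan requires correction, so the uncorrected figure is a best case. The medium within-group effect named in the Discussion has 56% and 37% in one arm of 20.

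These results rest on two-sided tests, on 0.5 as the meaning of moderate or medium, and on three tests as the correction. Higher power requires a larger assumed effect, such as the 1.0 SD difference in change behind f = 0.25, and even that falls to 74% at .05/3. A within-group effect in all PCT patients does similarly, but without a control arm.

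The baseline contrast does not share the attrition problem, although its detectable d of 0.70 uncorrected (0.81 at .05/3) is still above moderate. It would go too far to say that any positive BOLD result must be an overestimate, or that a null will be misread. Both are risks, and the present wording does nothing to reduce them.

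**What to change.** Remove the statement that 20 per group gives sufficient power for fMRI. For each BOLD comparison (baseline, randomised longitudinal, and PCT patients only), give the number expected to be analysable after drop-out and scan exclusion, and the effect detectable with it at the corrected threshold. If the scan-failure rate is unknown, give a range.

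Base the confirmatory BOLD test on a few a-priori contrasts drawn from the circuits in the Aims section, and label whole-brain results exploratory. State that a null longitudinal BOLD result does not exclude moderate effects.

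The cost is a rewording of the Sample size and MRI data sections and of the matching sentence in the Discussion. No patients are added. The downside is that the stated sensitivity becomes less favourable.
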